### Intervention (Aim 2)

The SCCCD intervention is a multicomponent, home-based program delivered by a pediatric occupational therapist trained in both the PAT curriculum and SCD care. Following our previously successful protocol [20], the intervention integrates 3 components during monthly home visits: OT to monitor and address developmental delays, the PAT curriculum to support caregivers in promoting developmental milestones and positive parenting, and SCD-specific education covering clinical recommendations such as medication adherence and protective behaviors (eg, hydration). Delivery by a single provider across all 3 components is intentional, as this approach establishes a high level of rapport between the family and the interventionist over the course of the program.

The intervention is adapted from our pilot study to be feasible within this population while maintaining sufficient dosage to observe change [20]. Families of infants under 9 months of age will be enrolled, and 12 monthly home visits will be offered over the course of 1 year [50-52]. In practice, we anticipate that some families will miss visits due to health-related concerns associated with SCD; therefore, the program may extend up to 15 to 18 months to ensure all children receive equivalent intervention dosage. In our prior work, maintaining frequent contact with families through their preferred communication method (eg, SMS) increased visit completion to 80% [20]. The PAT curriculum provides a developmentally appropriate activity and caregiver handouts for each visit. OT during visits will target specific developmental delays identified through ongoing evaluation, and SCD education will be reviewed and updated at each contact.

OT is uniquely suited to deliver this intervention given the combined expertise in mental health, rehabilitation, and child development. The proposed SCCCD intervention package, which combined OT, PAT, and SCD education, reflects a theoretically grounded, practically feasible approach to improving developmental outcomes in a population with both biological and environmental risk factors. The intervention will be discontinued if the family requests to stop services.

### Fidelity Monitoring

Interventionists will be trained to maintain adherence to the SCCCD protocol prior to delivering visits. Using the Comprehensive Intervention Fidelity Guide, the intervention design, training, and delivery will be systematically evaluated [53]. Fidelity will be documented through daily visit notes that capture completed activities, caregiver engagement, visit duration, handouts provided, SCD topics reviewed, and any additional caregiver training or referrals made [54,55]. Visits scheduled and completed will be tracked throughout the intervention period.

### Implementation Science Framework (Aim 3)

To identify determinants that influence caregiver participation in developmental screening and the SCCCD intervention, we will use a mixed methods (QUAL → quan) approach guided by the Consolidated Framework for Implementation Research 2.0 (CFIR) [56-58]. The CFIR is one of the most widely used frameworks for understanding contextual determinants in implementation research and has been recently updated with greater emphasis on including recipients of the intervention as key informants [56], making it well suited for a caregiver-centered inquiry.

Semistructured interviews will be conducted with up to 35 caregivers of children enrolled in aim 2, organized around 3 CFIR construct domains: outer setting (eg, health care system and community context), intervention characteristics (eg, acceptability and perceived fit of the SCCCD), and inner setting (eg, family and social support). We are confident that thematic saturation will be reached [35,59]. Qualitative themes from interviews will be integrated with quantitative participation data from aim 2—including visit completion rates, home visit duration, and family engagement—to provide a comprehensive characterization of the contextual determinants that facilitate or impede caregiver participation.

Interviews will be audio-recorded and transcribed verbatim. Two research team members will use an iterative inductive and deductive thematic analysis approach to review all transcripts and generate themes for a preliminary codebook [60]. The preliminary codes will be applied to 4 interviews using NVivo software (version 14; Lumivero) [61]; any deviations will be discussed, and the revised codebook will be applied to all remaining interviews [62]. Codes will be analyzed for themes, and participation data from aim 2 will be summarized [63,64].

### Data Analysis

#### Aim 1

Evaluations will be scored according to their respective manuals. Mixed effects regression will be used to analyze developmental outcome data, with time, group, and time-by-group interaction entered as fixed effects. This approach accounts for within-subject and within-group variability across the 3 longitudinal time points. Scores from the Bayley-4 will be compared to the ASQ-3. Covariates will include race, age, sex, caregiver education, socioeconomic status, disease-modifying medication use, and therapeutic intervention received. The number of evaluations completed and any therapeutic or behavioral interventions received (eg, physical therapy, OT, speech-language therapy) will be documented. Children who receive therapy services during the study period will be analyzed separately.

#### Aim 2

Standardized scores will be calculated for each assessment according to the respective manuals. Scores greater than 1 SD below the mean will be classified as a developmental delay. Repeated measures ANOVA will be used to compare group mean scores at 9, 18, and 30 months. Logistic regression will compare the number of children classified with a delay at 30 months to the aim 1 cohort. The number of caregivers approached and enrolled will be documented, and visits scheduled and completed, along with topics from visit notes, will be summarized. Additional analyses will examine possible changes in the home environment and caregiver mental health before and after the intervention. When the outcome is binary, a mixed effects logistic regression will be used, with time, group, and time-by-group interaction entered as fixed effects and variation of subject intercept as a random effect. Time will also be tested as a random effect in a more elaborate model.

#### Aim 3

Two research team members will use an iterative inductive and deductive thematic analysis approach to review all transcripts and generate themes for a preliminary codebook [60]. The preliminary codes will be applied to 4 interviews using NVivo software; any deviations will be discussed, and the revised codebook will be applied to all remaining interviews [62]. Codes will be analyzed for themes, and participation data from aim 2 will be summarized and integrated with qualitative findings [63,64].

The study protocol and deidentified data will be made available from the corresponding author on request and consistent with the NIH Data Management and Sharing Plan.

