Despite the high prevalence of developmental delay in this population, critical gaps remain. No study has prospectively characterized developmental trajectories across the first 3 years of life in children with SCD using a demographically matched comparison cohort and psychometrically robust assessment methods. Earlier work suggests that delays may worsen as children age [6,7,27], but this trajectory has not been rigorously evaluated. Additionally, no disease-specific intervention has been formally tested for infants and toddlers with SCD, and little is understood about the contextual factors that would support broader implementation of such a program. Because known environmental mediators of development—including socioeconomic status and disease severity—require comparison to well-matched peers, a prospective design with a demographically balanced comparison cohort is essential.

The purpose of this study is to determine the incidence and severity of developmental delays at 9, 18, and 30 months of age in children with SCD compared to demographically matched peers (aim 1); evaluate the effect of a 12-month, home-based SCCCD intervention on developmental outcomes in children with SCD (aim 2); and identify contextual determinants that facilitate or impede caregiver participation in developmental screening and home-based intervention, in preparation for future broader implementation (aim 3).

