### Participants

#### Aim 1: Incidence Cohort (n=100)

Children with SCD (n=50) under 9 months of age with all SCD genotypes and their caregivers will be recruited from the Sickle Cell Clinic at SLCH. Children without SCD (n=50) will be recruited as a comparison cohort and matched at the group level to the SCD cohort on the distributions of age, sex, race, socioeconomic status, and Area Deprivation Index [32], rather than paired individually. Group-level matching will be finalized after enrollment. Typically developing children will be recruited through SLCH general medicine, community early childhood centers, local pediatricians, public libraries, local early intervention providers, and faith-based organizations, using methods previously successful in this lab [33,34]. Children will be excluded if they have a diagnosis associated with developmental delay that is not attributable to SCD, or if the family is not English-speaking.

Caregivers of children with SCD will be approached by phone or following a regularly scheduled clinic visit. Interested caregivers will review the informed consent document with a member of the research team by phone, Health Insurance Portability and Accountability Act (HIPAA)–secure video call, or in person.

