### Measures

All outcome measures are summarized in Table 1. Demographic information will be collected from all participants at enrollment, including caregiver age, education, health literacy, marital status, household income, racial or ethnic identity, and number of children in the household. Clinical information collected for children with SCD will include SCD genotype, insurance status, hospitalizations and treatments, disease-modifying medication use, and neuroimaging results if available.

**Table 1. T1:** Summary of outcome measures.

Measure	Purpose	Type	Time point (months)	Aim
Bayley-4^a^	Child development	Clinician administered	9, 18, and 30	1 and 2
ASQ-3^b^	Child development	Caregiver report	9, 18, and 30	1 and 2
ITACS^c^	Child participation in family routines	Caregiver report	9, 18, and 30	1 and 2
BRIEF-P^d^	Executive functioning	Caregiver report	30 only	1 and 2
HOME^e^ Inventory	Home environment	Clinician observation	9, 18, and 30	2
PROMIS^f^ Depression (8 items)	Caregiver mental health	Caregiver report	9, 18, and 30	1 and 2
Semistructured interview	Implementation determinants	Interview	Ongoing	3

a Bayley-4: Bayley Scales of Infant Development, Fourth Edition.

b ASQ-3: Ages and Stages Questionnaires, Third Edition.

c ITACS: Infant Toddler Activity Card Sort.

d BRIEF-P: Behavior Rating Inventory of Executive Function-Preschool.

e HOME: Infant Toddler Home Observation for Measurement of the Environment.

f PROMIS: Patient-Reported Outcomes Measurement Information System.

The Bayley Scales of Infant Development, Fourth Edition (Bayley-4) is the primary outcome measure and has been the gold standard for evaluating and identifying developmental delay in children for over 50 years [25]. The Bayley-4 is completed in 45 to 60 minutes and evaluates 5 developmental domains: cognition, fine motor, gross motor, receptive language, and expressive language. Raw scores are converted to scaled scores, where a score of 10 indicates performance at the 50th percentile. A score greater than 1 SD below the mean will be classified as a developmental delay.

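### Adjusting the Aim 1 group comparison for disease-modifying medication, recorded only in children with SCD, turns the group effect into unmedicated SCD versus comparators

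*Protocol article*

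**What the plan says.** The Introduction states Aim 1 as follows: "determine the incidence and severity of developmental delays at 9, 18, and 30 months of age in children with SCD compared to demographically matched peers". The SCD cohort is not selected on treatment (Aim 1: Incidence Cohort): "Children with SCD (n=50) under 9 months of age with all SCD genotypes and their caregivers will be recruited". For the other arm of the comparison, "Children without SCD (n=50) will be recruited as a comparison cohort".

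Data Analysis, Aim 1, gives one model: "Mixed effects regression will be used to analyze developmental outcome data, with time, group, and time-by-group interaction entered as fixed effects". A few lines later it adds: "Covariates will include race, age, sex, caregiver education, socioeconomic status, disease-modifying medication use, and therapeutic intervention received". It describes no SCD-only model, no group-specific coding of medication and no standardised contrast.

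Measures shows who has the medication variable: "Clinical information collected for children with SCD will include SCD genotype, insurance status, hospitalizations and treatments, disease-modifying medication use, and neuroimaging results if available". No matching item is listed for comparison children.

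**The concern.** A covariate that varies in one group and is constant in the other changes what the group coefficient means. The medication coefficient is estimated within the SCD cohort alone, and the group coefficient becomes the difference at no medication. A reader would naturally take that coefficient as the SCD effect across all genotypes, because that is the aim and the cohort described.

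Nor does medication use look like a confounder of SCD versus no SCD. Since it is recorded as part of SCD care, it most plausibly follows from having the disease. At stake are the meaning of the main between-group estimate and some of its precision, with only 50 children per group.

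**Working it through.** **Inputs from the document.** 50 children with SCD and 50 without; visits at 9, 18 and 30 months; fixed effects for time, group and their interaction; medication use listed as a covariate and collected in the SCD cohort. The article gives no medicated share, effect size or power figure for Aim 1, so there is no stated result to reproduce.

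**Assumptions.** Comparison children have no disease-modifying medication (inferred from the cohort definition and Measures, not stated). The SD of a scaled score is 3; the article gives only the centre of the scale ("Raw scores are converted to scaled scores, where a score of 10 indicates performance at the 50th percentile"). The medicated share p and the medication coefficient b2 are varied.

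**Step 1: what the coefficient estimates.** At one visit write Y = b0 + b1·G + b2·M, with G = 1 for SCD, M = 1 if medicated, and M = 0 for every comparator. Then:

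- b1 = E[Y | SCD, unmedicated] − E[Y | comparison]
- all-SCD contrast = b1 + p·b2
- shift caused by the covariate = −p·b2

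Centring M at the grand mean leaves b1 unchanged. Centring it within the SCD cohort, or averaging over that cohort's medication use, recovers the all-SCD contrast. If M is missing for comparators, a complete-case fit loses all of them.

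**Step 2: the shift can go either way.**

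*Medicated children score better.* Take an unmedicated deficit of 2.0 points, so b1 = −2.0.

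- p = 0.2, b2 = 0.5: all-SCD contrast −2.0 + 0.1 = −1.9
- p = 0.5, b2 = 1.0: −2.0 + 0.5 = −1.5
- p = 0.8, b2 = 1.5: −2.0 + 1.2 = −0.8

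The adjusted model reports −2.0 each time, overstating the all-SCD deficit by 0.1 to 1.2 points.

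*Sicker children are medicated, no drug effect.* Take 60% severe with a 3-point deficit, 40% milder with a 1-point deficit, and 10% of the milder medicated. The all-SCD deficit is 0.6×3 + 0.4×1 = 2.2. The deficit among the unmedicated is:

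- 50% of severe medicated: (0.30×3 + 0.36×1)/0.66 = 1.26/0.66 = 1.91
- 70%: (0.18×3 + 0.36×1)/0.54 = 0.90/0.54 = 1.67
- 90%: (0.06×3 + 0.36×1)/0.42 = 0.54/0.42 = 1.29

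Here the adjusted model understates the deficit by 0.29 to 0.91 points.

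**Step 3: precision at one visit.** Without the covariate, SE = 3·√(2/50) = 0.60. With it, SE = 3·√(1/50 + 1/(50(1−p))):

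- p = 0.2: 3·√0.045 = 0.64 (variance ×1.12)
- p = 0.5: 3·√0.060 = 0.73 (×1.5)
- p = 0.8: 3·√0.120 = 1.04 (×3.0)

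**Step 4: the three-visit mixed model.** Simulations used random intercepts, 50 versus 50 children and 100 replicates per scenario. The group effect is at 9 months; the time-by-group term is the extra change by 30 months.

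- Medication fixed over time (p = 0.5, b2 = +1): group effect −1.53 without the covariate, −2.10 with it; time-by-group term −0.94 in both.
- Medication rising from 20% to 50% to 80% over the visits (b2 = +1): time-by-group term −0.40 without, −0.97 with.
- The more severe half medicated throughout, with a drug benefit of 1 point: group effect −1.48 without, −0.74 with; time-by-group term −1.01 in both.

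**The case against.** The article is condensed. Its covariate sentence does not say that every listed variable enters one model together, and it gives no coding or reported contrast. A fuller analysis plan could restrict medication to an SCD-only model, centre it within the SCD cohort or standardise the contrast. That is possible, but group is the only exposure named and no SCD-only model is described. The covariate is affirmatively listed, so this is not a detail left for later.

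It is also fair that no sentence says that comparison children cannot receive such medication. This is an inference, though a strong one.

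A sponsor might instead want the deficit in the absence of treatment. No such target is stated. If treatment tracks severity, adjusting for treatment alone would not deliver it, and genotype is collected but not among the listed covariates.

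A reader might infer that the SCD effect will be biased toward zero. The documents do not support this: they give neither the medicated share, nor who is treated, nor how treated children score, and step 2 shows both signs. A reader might also infer that the developmental trajectories are distorted. That follows only if medication starts or changes during follow-up. Finally, unadjusted counts of delay by group are not affected.

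**Conclusion.** The point holds as a mismatch between model and aim. As written, the Aim 1 group coefficient answers a question about unmedicated children with SCD, while the aim and the recruitment cover all of them. This rests on medication being zero in comparators; if it is left missing, the complete-case consequence is worse.

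The size is p·b2. Under the illustrative inputs it runs from an overstatement of 1.2 points to an understatement of 0.91 points, and it vanishes if b2 is zero. These figures show what is possible and do not predict this cohort. The precision loss does not depend on the sign: the SE goes from 0.60 to between 0.64 and 1.04 for medicated shares of 20% to 80%, given an SD of 3 and a single visit. Confidence is high for the change in what is estimated, and none is claimed for its direction.

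**What to change.** In Data Analysis, Aim 1, remove disease-modifying medication use from the SCD-versus-comparison model. The other listed covariates are left as they are by this point. Add a secondary model limited to children with SCD that examines medication use together with genotype, which is already collected.

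Alternatively, keep medication in the model, code it explicitly as zero for comparators, and report the group contrast standardised to the SCD cohort's observed medication use at each visit. State that this standardised contrast is the Aim 1 estimate.

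Either change costs only wording in the analysis section. It needs no new data, and enrolment for Aim 1 is still under way.

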### Procedures

Developmental evaluations will be conducted at 9, 18, and 30 months of age (±1 month) for children enrolled in both aim 1 and aim 2. Evaluations will take place in a dedicated child-friendly testing room on the Washington University School of Medicine campus, which has a padded floor, child-safe furniture, and space for caregivers to sit comfortably. Five accessible parking spots are reserved directly in front of the testing room, and the space is located within a 5-minute walk of public transportation. Visits will last approximately 60 to 90 minutes. Snacks will be provided to support child engagement during the evaluation, and caregivers will be compensated for their time and travel at each visit. Following institutional review board (IRB) amendment, evaluations may also be conducted in the family’s home for participants residing within the Greater St. Louis Metro area, in response to caregiver feedback regarding barriers to on-site attendance. Any changes are communicated to participants and shared with our community advisory board.

Demographic information and caregiver surveys will be collected using REDCap, a HIPAA-secure web-based data capture system, administered on a research tablet [36,37]. Survey data may also be completed by caregivers remotely via a secure web-link before or after the visit to reduce in-person visit burden. Assessors will be trained to maintain adherence to the evaluation protocol prior to data collection. Following each evaluation, the assessor will prepare a written summary report of the child’s developmental scores, review the results with the caregiver, and share the report with the child’s pediatrician and hematologist at the family’s request. If a developmental delay is identified (>1 SD below the mean), the research team will discuss the results with the caregiver and offer a referral to Early Intervention services, the federally funded, state-administered early intervention program available to eligible children under 3 years of age at no cost to families [38,39].

Retention strategies include SMS text message reminders prior to each scheduled visit; flexible scheduling, including early morning, evening, and weekend appointments; and reimbursement for parking or public transportation. Text message reminders have been effective in reducing visit cancelations in our prior work [20].

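### Aim 1 conditions on therapy that the study's own finding of delay can set in motion, by covariate and by separate analysis of recipients, and this biases its estimates

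*Protocol article*

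**What the plan says.** All places are in the Protocol article. Under Procedures, when an evaluation shows a score more than 1 SD below the mean, "the research team will discuss the results with the caregiver and offer a referral to Early Intervention services". Under Measures, the outcome uses the same cut: "A score greater than 1 SD below the mean will be classified as a developmental delay".

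Under Data Analysis, Aim 1, the mixed model is specified "with time, group, and time-by-group interaction entered as fixed effects". Then: "Covariates will include race, age, sex, caregiver education, socioeconomic status, disease-modifying medication use, and therapeutic intervention received". Two sentences later: "Children who receive therapy services during the study period will be analyzed separately".

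The article says that therapies received will be documented. It does not say whether the separate analysis replaces or supplements the main one, or what happens to evaluations made before therapy began. The Introduction reports that in the team's earlier cohort 50% of children with SCD older than 12 months were delayed and none was receiving therapy. It also cites a guideline range of 30% to 50%.

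**The concern.** Therapy started during the study is not a baseline characteristic. A child found delayed at 9 or 18 months is offered a route to therapy because of that finding. No child in the earlier SCD cohort was in therapy, so much of the therapy in this cohort would plausibly follow the study's own evaluations. Adjusting for therapy, or setting recipients aside, therefore conditions on a consequence of an earlier value of the primary outcome.

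Aim 1 is meant to establish how often and how severely delay occurs, and how this differs between cohorts over time. Setting recipients aside takes out children whom the aim is meant to count. Adjusting for therapy holds fixed a marker of earlier low scores and so absorbs part of the group difference. If a child's whole record is set aside, the 9-month rate is affected too, although 9-month scores precede any therapy that the study prompts.

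**Working it through.** The article gives no power calculation or effect size for aim 1, so there is no stated figure to reproduce. The check is of direction and rough size.

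**Do the two statements fit together?** If recipients leave the main model, therapy received takes one value for everyone left and cannot act as a covariate. If they stay, the separate analysis is an addition and only the covariate acts on the main model. The text does not say which is meant.

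**Delay rate if recipients are left out.** Let p be the true delay rate, u the therapy uptake among delayed children and v the uptake among the others. If delay persists and therapy has no effect,

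retained rate = p(1−u) / [p(1−u) + (1−p)(1−v)].

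This is below p exactly when u > v.

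Inputs from the article: p = 0.50 for SCD, with 0.30 as the lower end of its range. Assumed: p = 0.15 in the comparison cohort, v = 0.03, and u = 0.2, 0.4 or 0.6, equal in both cohorts.

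- SCD, p = 0.50: 0.400/0.885 = 45.2%; 0.300/0.785 = 38.2%; 0.200/0.685 = 29.2%.
- SCD, p = 0.30: 0.240/0.919 = 26.1%; 0.180/0.859 = 21.0%; 0.120/0.799 = 15.0%.
- Comparison, p = 0.15: 0.120/0.9445 = 12.7%; 0.090/0.9145 = 9.8%; 0.060/0.8845 = 6.8%.

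Group difference:

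- from 50 − 15 = 35 points to 32.5, 28.4 or 22.4;
- from 30 − 15 = 15 points to 13.4, 11.1 or 8.2.

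**Unequal uptake.** With u = 0.2 in SCD and 0.6 in the comparison cohort, the difference is 45.2 − 6.8 = 38.4 points, above the true 35. With u = 0.6 in SCD and 0.2 in the comparison cohort, it is 29.2 − 12.7 = 16.5 points. So the direction depends on relative uptake.

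**Scores.** A simulation used 400,000 children, scaled scores with SD 3 and comparison mean 10, delay below 7, within-child correlation 0.6, and therapy only after delay at 9 or 18 months. It analyzed the 30-month score, not the full three-visit model, so it shows direction and rough size only. Group differences in scaled points:

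| True difference | Uptake (SCD / comparison) | Recipients removed | Therapy as covariate |
|---|---|---|---|
| 3.0 | 25% / 25% | 2.8 | 2.7 |
| 3.0 | 50% / 50% | 2.5 | 2.3 |
| 3.0 | 75% / 75% | 2.1 | 2.0 |
| 3.0 | 25% / 75% | 3.2 | 2.9 |
| 1.5 | 25% / 75% | 1.8 | 1.65 |

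These values hardly changed for therapy effects of 0, 1 or 2 points. With a true difference of 3.0 and equal uptake of 25%, 50% or 75%, removing whole records also lowered the 9-month SCD delay rate from 50% to 40%, 28% or 13%.

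**The case against.** **The separate analysis may not mean removal.** A reader might infer that recipients are certainly dropped from the main analysis. The text does not say so. Because therapy is also a covariate, it can be read as one model for all children plus an added subgroup. On that reading the internal conflict and the reduced delay rates disappear. This objection stands as far as it goes, but the covariate still acts on the main model.

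**The group difference need not shrink.** A reader might infer a downward bias in every case. The article gives reasons why uptake could differ between cohorts: it notes under-diagnosis in minoritized groups, it recruits comparison children partly through early intervention providers, and at the interim 15 of 24 comparison children are White while 25 of 26 children with SCD are Black or African American. The direction is therefore open.

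**The study offers a referral, not therapy.** Acceptance and eligibility are unknown, and therapy can start for other reasons. This limits the size of the bias, for which the article gives no uptake figure.

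**Development without therapy is a legitimate target.** True, but neither step estimates it. In the simulation with 50% uptake and a 1-point therapy effect, the no-therapy difference is 3.0. Keeping all children gives 2.75, removal 2.5 and the covariate 2.3. With a 2-point effect the three are 2.5, 2.5 and 2.3.

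**Aim 2.** A reader might infer that the filter also flatters the aim 2 comparator. The article compares with the aim 1 cohort and states no such filter, so this does not follow.

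**Conclusion.** The point holds in this form. Therapy during the study is partly a consequence of the outcome at an earlier visit, and the plan conditions on it, certainly by covariate and possibly also by removal. If removal is meant, the two statements contradict each other.

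- **Delay rates**, if recipients are left out, are understated in each group whenever delayed children take up therapy more often than non-delayed children. At 20%, 40% or 60% uptake, a true SCD rate of 50% becomes about 45%, 38% or 29%, and a true 30% becomes about 26%, 21% or 15%.
- **The group difference** is biased under either step. It moves toward zero if uptake among delayed children is similar in both cohorts or higher in SCD. It may be unchanged or inflated if uptake is higher in the comparison cohort.

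The SCD rates are the article's. The comparison rate, all uptake values, the within-child correlation and the therapy effects are assumptions.

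**What to change.** - Define the primary aim 1 analysis as including every evaluated child regardless of therapy, and remove therapy received from its covariates.
- State that the estimate is for development under the study's own referral practice.
- Report therapy uptake by group and visit.
- Recast the separate analysis as a labelled sensitivity analysis that keeps all pre-therapy evaluations and drops only later scores. A likelihood-based mixed model can accommodate scores dropped in this way if therapy uptake depends on the earlier scores and covariates in the model.

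The cost is mainly wording, and with 50 of 100 aim 1 children still to be recruited the change can precede the final analysis. Two costs should be acknowledged. First, any benefit of therapy becomes part of the estimate: with an assumed 1-point effect and 50% uptake, the 30-month rates would be 44% and 14% instead of 50% and 16%. Second, the sensitivity analysis needs therapy start dates, or at least therapy status at each visit. The article says only that therapy will be documented, so the sponsor should confirm that timing is captured.
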